## Exclusion criteria

A potential subject who meets any of the following criteria will be excluded from participation in this study:

- Acute illness or current evidence of acute or chronic inflammatory or infective diseases
- Abusive alcohol use (> 21 IU/week for men, > 14 IU/week for women)
- Diagnosed liver cirrhosis and/or hepatocellular carcinoma
- Diagnosed cardiorespiratory, neurological or musculoskeletal disease
- Diagnosed insulin or GLP-1 agonist treated type 2 diabetes or type 1 diabetes
- Hepatitis B and/or C or auto-immune hepatitis
- Wilsons disease/alpha-1-antitripsine deficiency
- Hemochromatosis
- Untreated hypothyroidism
- Lipoatrophy
- Bleeding disorder or anti-coagulant use which cannot be temporarily discontinued
- Not able or willing to undergo MRI (for example claustrophobia, ICD, pacemaker)
- Diagnosed depression or any mental illness rendering the patients unable to understand the nature, scope and possible sequences of the study
- Any participation in regular exercise and/or diet program more than 2 times per week in the 3 months prior to recruitment

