## Inclusion criteria

In order to be eligible to participate in this study, a subject must meet all of the following criteria:

- Diagnosis of steatosis on transient elastography, conventional ultrasound, magnetic resonance imaging, computed tomography, liver biopsy, or identified as steatotic subject by fatty liver index (FLI) algorithm which is based on waist circumference, body mass index, and levels of triglyceride and γ-glutamyltransferase (Koehler et al. 2013).
- 18-70 years of age
- BMI < 40 kg/m^2^

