### Liver biopsies

The ultrasound-guided liver biopsy will be performed at baseline and endpoint visits as previously described (2013_207). If a liver biopsy is already performed 12 months prior to screening, no need for baseline biopsy. After an overnight fast, the subject will be in supine position, and using an ultrasound a non-vascularised segment of the right liver lobe will be identified. A needle of 14 to 19 gauge will be used for the biopsy, and the patient will be asked to hold their breath during the biopsy. Afterwards a bandage will be put on the puncture site. The total estimated time for the biopsy is 15-30 minutes. The subject is then instructed to lie on his/her right side for 1-2 hours after the test, and pulse, blood pressure and temperature are checked after the biopsy. All samples will be stored both in formalin/paraffin and frozen in liquid nitrogen after extraction, and stored at -80°C until analysis. Ultrasound-guided percutaneous liver biopsy is a safe method at our hospital with a low complication rate (typically self-limiting bleeding) of less than 0.1% (Sporea, Popescu, & Sirli, 2008).

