### Serious adverse events (SAEs)

A serious adverse event is any untoward medical occurrence or effect that

- results in death;
- is life threatening (at the time of the event);
- requires hospitalisation or prolongation of existing inpatients’ hospitalisation;
- results in persistent or significant disability or incapacity;
- is a congenital anomaly or birth defect; or
- any other important medical event that did not result in any of the outcomes listed above due to medical or surgical intervention but could have been based upon appropriate judgement by the investigator.

An elective hospital admission will not be considered as a serious adverse event.

The investigator will report all SAEs to the sponsor without undue delay after obtaining knowledge of the events.

The sponsor will report the SAEs through the web portal *ToetsingOnline* to the accredited METC that approved the protocol, within 7 days of first knowledge for SAEs that result in death or are life threatening followed by a period of maximum of 8 days to complete the initial preliminary report. All other SAEs will be reported within a period of maximum 15 days after the sponsor has first knowledge of the serious adverse events.

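### Section 4.3 does not exclude pregnancy at entry, so a pregnant woman is eligible for tissue biopsies and exhaustive exercise in a single-arm before-after study

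*Protocol*

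**What the plan says.** Section 4.2 has three inclusion criteria: steatosis by one of several methods, a BMI below 40 kg/m², and "18-70 years of age". None restricts sex. One permitted route to the steatosis criterion is the fatty liver index, which is computed partly from waist circumference and BMI.

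Section 4.3 begins "A potential subject who meets any of the following criteria will be excluded from participation in this study" and lists 14 items. One of them, "Abusive alcohol use (> 21 IU/week for men, > 14 IU/week for women", gives a limit for women, so women are plainly expected to enrol. The item nearest to pregnancy is "Not able or willing to undergo MRI (for example claustrophobia, ICD, pacemaker". No item names pregnancy, childbearing potential or a pregnancy test.

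On procedures, section 6.3.13 states "The ultrasound-guided liver biopsy will be performed at baseline and endpoint visits", with the exception "If a liver biopsy is already performed 12 months prior to screening, no need for baseline biopsy". Sections 6.3.14 and 6.3.15 add muscle and subcutaneous fat biopsies at both time points, section 6.3.4 a cycle test to exhaustion at baseline and after 12 weeks, and section 5.1 twelve weeks of high-intensity intervals.

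Section 6.2 (randomisation) is marked not applicable, and section 8.1 bases the primary analysis on the comparison of baseline with endpoint.

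**The concern.** Eligibility is fixed by the protocol, and a later analysis plan would not normally supply it. A recruiter who applies sections 4.2 and 4.3 exactly as written has no ground to turn away a woman who is pregnant at screening. Two things are at stake.

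The first is avoidable exposure. She would enter a study of invasive tissue sampling and maximal exercise without the protocol having considered her condition. The risk assessment in section 9.3 covers the cannula and the liver, fat and muscle biopsies, and does not mention pregnancy.

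The second is interpretation. The design has one arm and compares each subject with herself. It therefore cannot separate a change due to exercise from one due to anything else that moves over the same 12 weeks. Section 5.1 asks subjects to hold weight steady, and section 6.1.3 collects weight and body composition as possible confounders. A continuing pregnancy works against that premise. Entry through the fatty liver index could also be affected, because two of its components are body-size measures.

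**Working it through.** No formula in the plan bears on this point and there is no stated figure to reproduce. The check is a reading of every provision that might exclude or detect a pregnancy present at entry.

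**Could another provision close the gap?**

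| Provision | What it reaches | Pregnancy present at entry? |
| --- | --- | --- |
| 4.2 inclusion | Age, BMI, steatosis; either sex | Admitted |
| 4.3, acute illness and inflammatory or infective disease | Illness | Not a natural reading of pregnancy |
| 4.3, MRI criterion | Anyone unable or unwilling to be scanned; the examples are illustrative | Might exclude some women in practice; does not name pregnancy and prompts no check |
| 6.4, withdrawal by the investigator | Urgent medical reasons | Discretionary; depends on the pregnancy being known and on that judgement |
| 6.4.1, withdrawal criteria | A condition new during the study that needs admission, changes prescriptions or is likely to affect the outcome; also failure to follow instructions | A condition present at entry is not new |
| 7.2.2, SAE definition | "is a congenital anomaly or birth defect; or" | Reporting after the event; does not act on entry |
| 9.3, risk assessment | Cannula and biopsy risks | Not mentioned |

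No row excludes a pregnancy present at entry, and none requires that it be looked for.

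**What would such a subject undergo?** Normally two percutaneous liver biopsies, or one within the study if a biopsy from the preceding 12 months replaces the baseline one. In addition: muscle and fat biopsies at both time points, MRI sessions of about 60 minutes (6.3.7), two tests to exhaustion, and two supervised interval sessions a week for 12 weeks.

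**How much weight would one case carry?**

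- Inputs: 15 subjects in the first part and another 15 if extended, so 30 in all (sections 3 and 4.4).
- Share of the sample: 1/15 = 6.7%; 1/30 = 3.3%.
- If pregnancy adds an amount *d* to her baseline-to-endpoint change in some measure, the mean change moves by *d*/n, which is 0.067*d* with n = 15 or 0.033*d* with n = 30.

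The documents give no value for *d*, so the arithmetic stops there. That pregnancy can move weight, waist and metabolic measures is taken as general knowledge and is not a figure from the protocol.

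**How often would it happen?** This cannot be computed from the documents. They give no expected sex ratio, no age distribution within 18 to 70, and no figure for pregnancy at screening.

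**The case against.** The best defence is that the practical risk is small and that some protection exists.

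- **Pregnancy arising during the study.** Section 6.4.1 withdraws subjects with a new condition likely to affect the outcome, and section 6.5 replaces them. This can plausibly reach such cases once they are known. That stands, and it confines the point to pregnancy present at entry.
- **MRI criterion.** Its list is introduced as examples, so a reader who takes it to cover only claustrophobia and implants reads too much into it. That stands. It still names no pregnancy criterion, and a woman unaware that she is pregnant is neither unable nor unwilling to be scanned.
- **Unseen material.** Section 9.2 places the patient information letter in a separate document, which may address pregnancy. Investigators may also ask informally. Both are possible, but neither amends section 4.3.
- **Main endpoints.** Section 6.1.1 rests on liver biopsy, MRI/MRS, histology and gene expression. Weight and resting energy expenditure are other parameters, and microbiota is secondary. A reader might infer that the primary result would be biased. The documents do not show this; the supported claim concerns weight, waist and metabolic measures.

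Three further inferences are not supported. An annual pregnancy rate multiplied by study duration would count pregnancies that begin during follow-up, which is a different event from the gap described here. The congenital-anomaly line belongs to a general SAE definition and does not show that the authors foresaw this risk. Nor are the biopsies without clinical use: the Summary says that a baseline finding of NASH leads to referral for follow-up and dietary counselling.

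**Conclusion.** The point holds for pregnancy present at entry. The eligibility rule as written admits a pregnant woman to biopsies and exhaustive exercise, and no other supplied text excludes or detects her condition. Because there is no control arm, any pregnancy-related change in her weight, waist or metabolic measures would be counted as change on exercise.

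The event should be rare, and no reliable frequency can be given. If it occurs, one case is 6.7% of 15 subjects or 3.3% of 30. The main reason to act is participant safety; the effect on the data is secondary and its size is unknown.

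The conclusion assumes that the exclusion list is complete as supplied. It appears unbroken and shows no sign of redaction. A reader might go further and infer that all subjects have two study biopsies, that breastfeeding should be treated in the same way, or that a pregnancy during the study is wholly unprovided for. The documents support none of these.

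**What to change.** Add current pregnancy to the exclusion criteria in section 4.3. State that it is ascertained at screening, in women of childbearing potential, before any biopsy, MRI or exercise test. Ask the sponsor to clarify whether a pregnancy discovered during the study counts as a new condition under section 6.4.1. How such a case should be managed is for the sponsor and the ethics committee, and no rule is proposed here.

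The cost is one line in the protocol and one screening question or test for the women concerned, with negligible effect on recruitment. If the first part has already enrolled, the change would still apply to the additional 15 subjects foreseen in section 3.

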There are currently no pharmacological treatment options to treat NAFLD or to prevent its progression to NASH, NAFL-related fibrosis, or cirrhosis (Oseini & Sanyal, 2017; Ratziu, 2017). According to the European Association for the Study of the Liver (EASL), European Association for the Study of Diabetes (EASD), and the European Association for the Study of Obesity (EASO) (2016) the internationally recommended therapies include physical exercise and dietary modifications. Mainly, weight reduction through lifestyle interventions is the target to prevent NAFLD progression. It is stated in the guideline that 7-10 % weight reduction is recommended for NAFLD patients. Previously published intervention studies have investigated the effect of weight reduction through a combination of diet, exercise and behavioural interventions on the disease (Promrat et al., 2010; Vilar-Gomez et al., 2015). Results are still inconsistent whether weight loss is sufficient therapy in advanced stages of NASH whereas in steatosis even a small weight loss is beneficial for reducing liver fat and insulin resistance (Ratziu, 2017). However, weight reduction and its sustainability are more complicated in real-life clinical practice than seen in research intervention trials with intense guidance and follow-ups. Most of the obese patients who manage to lose weight successfully tend to regain most of it in the first 3 years. In addition to the difficulties related to weight management in health care, lifestyle interventions require a lot of investment and knowledge among health care professionals. Due to these matters it would be necessary to identify which specific lifestyle intervention would be the most effective to prevent the progression of NAFLD to increase efficacy, adherence and motivation.

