# TREATMENTS OF SUBJECTS

## Treatment

The intervention group will follow a high-intensity interval training (HI) protocol on a cycle ergometer (Hallsworth et al., 2015). To determine the intensity of the individually prescribed training program and the efficacy of the exercise intervention, ergospirometry tests will be performed in collaboration with the department of Cardiology AMC ([name]) that has all expertise to execute this study. The training sessions and ergospirometry tests will be carried out in Polifysiek, Hogeschool van Amsterdam. Furthermore, physical activity of study subjects will be monitored through the intervention by questionnaires. These are described later in the chapter of study procedures. Subjects are asked to keep their diet and weight unchanged.

The exercise intervention will start immediately after the ergospirometry test. In detail, the concept of HI involves repeated bouts of exercise at an intensity of 85 % of W_max4_ interspersed by recovery periods based on a baseline ergospirometry test. W_max4_ refers to the hypothetical workload sustainable for 4 min (Tornvall G, 1963). While being hypothetical, W_max4_ is useful for defining the presumably optimal intensity for work intervals at HI. The intervention group will perform HI session involving 5 bouts of 2-4 minutes work intervals (at 85 % of W_max4_) interspersed by 3 minutes of active recovery (at 10 % of W_max4_) period twice per week on non-consecutive days for 12 weeks. Each work interval will be 2 minutes long in the first week with 5 seconds added per each exercise session (i.e. 10 seconds per week) so that HI intervals will be 4 minutes long by week 12. If the subject fails to complete the work interval, he/she will still be instructed to continue the exercise session by starting the following scheduled work interval(s) after the recovery period(s). At the beginning of the intervention period, each HI session will last approximately 40 minutes, including warm-up (at 30% of W_max4_), recovery periods and cool-down (at 20 % of W_max4_). At the end of the intervention period, each HI session will last approximately 50 minutes. HI will be conducted in a group of 1-3 subjects closely supervised by exercise physiologist, or some other qualified health care professional (e.g. biomedical laboratory scientist) adequately trained for the task.

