Additionally, an individualized exercise training program will be prescribed for each subject in the HI group consisting of home-based low-to moderate-intensity aerobic exercises. An overall weekly goal, including supervised exercise, will be three hours of aerobic exercise e.g. walking, swimming and cycling following international guidelines (US GUIDELINE 2018). Exercise training program is described in details in table 1.

Table 1. Exercise training program in high-intensity aerobic interval group.

| Study weeks | **0–4** | **5-8** | **9-12** |
| --- | --- | --- | --- |
| *High-intensity aerobic interval training* |  |  |  |
| Duration of warm-up, min | 10 | 10 | 10 |
| High-intensity interval training frequency/week | 2 | 2 | 2 |
| Intensity of work phase, % W_max4_ | 85 | 85 | 85 |
| Intensity of recovery phase, % W_max4_ | 10 | 10 | 10 |
| Interval sets, number | 5 | 5 | 5 |
| Duration of the interval, seconds | 120-160 | 160-200 | 200-240 |
| Recovery between sets, minutes | 3 | 3 | 3 |
| Intensity of warm-up, % W_max4_ | 30 | 30 | 30 |
| Intensity of cool-down, % W_max4_ | 20 | 20 | 20 |
| Duration of cool-down, min | 5 | 5 | 5 |
| *Additional home-based aerobic training* |  |  |  |
| Duration, min/week | 140 | 120 | 100 |

W_max4_ refers to the hypothetical workload sustainable for 4 minutes.

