### Dietary intake

The subjects will get instructions to keep their diet unchanged. Online dietary intake lists will be taken as previously described (voedingscentrum.nl). Online 4-day dietary lists are taken just before the intervention period at baseline, and 5-day dietary lists are taken midway and at the end of the intervention. The online dietary intake lists will be recorded during predefined consecutive days (3-4 weekdays, 1 weekend day) and checked by researchers.

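### Section 4.3 screens diet programmes by weekly frequency, so it can admit subjects in an ongoing weight-loss programme whose effect this uncontrolled before-after design cannot separate from exercise

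*Protocol*

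**What the plan says.** Section 4.3 of the protocol excludes "Any participation in regular exercise and/or diet program more than 2 times per week in the 3 months prior to recruitment". Participation up to and including twice a week is therefore allowed, for exercise and for diet programmes alike. Neither section 4.2 nor section 4.3 asks for stable weight before entry.

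Section 5.1 prescribes supervised interval sessions "twice per week on non-consecutive days for 12 weeks". At the start, "each HI session will last approximately 40 minutes"; by the end, "each HI session will last approximately 50 minutes". Work intervals run at 85% of Wmax4. Table 1 adds home-based training of 140, 120 and 100 minutes a week across the three blocks, and the text sets an overall goal of three hours a week. The same section asks subjects to hold both diet and weight constant. Section 6.3.2 repeats the diet half: "The subjects will get instructions to keep their diet unchanged".

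Section 6.1.3 lists body weight (three times), body composition (twice) and dietary lists as potential confounders, and says the lists are used to look for changes in habits. Section 6.2 states that randomisation and allocation do not apply. Section 8.1 compares baseline with endpoint by a one-sample t-test or a chi-square test and names no covariate. The Introduction accepts that "in steatosis even a small weight loss is beneficial for reducing liver fat and insulin resistance".

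**The concern.** The rationale in section 1 is the effect of exercise on the liver apart from weight change. In a single-arm before-after study, anything else that moves the liver over the 12 weeks is read as effect, so the entry criteria carry much of the protection against bias.

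For exercise, sessions per week is a rough but meaningful measure. For diet it is not, because a programme attended once a week may govern every meal. An outpatient with fatty liver who attends such a programme passes section 4.3, is told to leave the diet alone, and may go on losing weight and liver fat through the intervention. That change would inflate the apparent effect of exercise. It would also bear on the interim look at 15 subjects, which section 4.4 uses to decide whether 30 are needed.

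**Working it through.** **1. What the rule lets through.** Excluded: more than 2 times a week. Eligible: 0, 1 or 2 times a week, for either kind of programme.

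**2. The diet part, set against the other sections.**
- *Section 5.1 (diet and weight constant).* A subject losing weight on a continuing diet cannot meet both halves. Continuing the diet changes weight; holding weight means changing the diet.
- *Section 6.3.2 (diet unchanged).* Taken alone, this tells that subject to carry on with the weight-loss diet.
- *Section 6.1.3 (dietary lists look for change).* A diet begun before the first list and continued shows no change, so the lists would not flag it.
- *Section 6.1.3 (serial weights).* These would show ongoing loss, but only after enrolment and the baseline biopsies. They cannot say whether diet or training caused it.
- *Sections 6.2 and 8.1.* There is no control arm and no named adjustment.

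**3. Size of the diet part.** Let d be the extra change in a subject due to the diet, and k the number of such subjects among n = 15. The cohort mean shifts by k × d / 15, that is, d/15 (6.7% of d) for one subject and 3d/15 = d/5 (20% of d) for three. The documents give neither k nor d, so the bias cannot be put on the outcome scale.

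**4. The exercise part: the plan's own figures first.** From Table 1, session length = warm-up + 5 work intervals + 5 recoveries + cool-down.
- Start: 10 + 5 × 2 + 5 × 3 + 5 = 40 min. This reproduces the stated 40.
- End: 10 + 5 × 4 + 5 × 3 + 5 = 50 min. This reproduces the stated 50.

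At two sessions a week, supervised time is 80 to 100 min. Adding home training:
- weeks 0–4: 80.0 to 86.7, plus 140 = 220.0 to 226.7 min;
- weeks 5–8: 86.7 to 93.3, plus 120 = 206.7 to 213.3 min;
- weeks 9–12: 93.3 to 100.0, plus 100 = 193.3 to 200.0 min.

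The programme is therefore about 193 to 227 min a week on Table 1, or 180 min on the stated goal. Two prior sessions a week equal the supervised frequency, but nothing makes them equal this total or the 85% Wmax4 intensity.

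**5. Illustration of dilution (assumed inputs).** Let f be the share of entrants already trained and r their response relative to untrained entrants. Mean reduction = 25% × [1 − f(1 − r)], where 25% is the reduction in section 4.4.

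| f (assumed) | r = 0 | r = 0.5 |
| --- | --- | --- |
| 10% | 22.5% | 23.8% |
| 20% | 20.0% | 22.5% |
| 30% | 17.5% | 21.3% |

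I do not carry this into power. Section 4.4 gives no standard deviation or proportions, so its figure of 28 cannot be rebuilt uniquely.

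**The case against.** The strongest reply on diet is that the phrase is ambiguous. If a time means a day of following the diet, a daily dieter exceeds two a week and is already excluded. That reading is possible, but participation in a programme a number of times a week more naturally means attendance. A criterion that admits or excludes the same person depending on the reading needs rewording either way.

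Second, safeguards exist outside section 4. Section 5.1 asks for constant weight, section 6.4.1 withdraws subjects who do not follow instructions, and researchers check the dietary lists. These stand as partial protection. They act after entry, and the lists are aimed at change. A statistical analysis plan, not at hand, might also add an adjustment for weight; in a single arm that could not tell diet-driven loss from training-driven loss.

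Third, a reader might infer that twice-weekly exercisers arrive already treated, because 2 − 2 = 0 added sessions. The objection to that succeeds. Frequency is not dose: Table 1 adds home training, the workload is set from each subject's own baseline test, and the intervals lengthen from 2 to 4 minutes. Prior training would also tend to shrink the measured change, which is the conservative direction. Where to set the exercise cut-off is largely the sponsor's preference.

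Finally, rewording one criterion does not cure the lack of a control group. That is true, but it removes one foreseeable source of bias that the design cannot otherwise handle.

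**Conclusion.** The point holds for diet programmes and only weakly for exercise.

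- *Diet.* Section 4.3 can admit a subject in an ongoing weight-loss programme, and the planned comparison cannot separate that subject's continuing change from the exercise effect. This rests on reading the frequency as attendance. Each such subject carries 1/15 of the cohort mean; the number of subjects and the diet's own effect are not in the documents.
- *Exercise.* Dilution is possible but not shown. With 20% of entrants assumed already trained and responding at 0 to 50% of the untrained response, a 25% reduction becomes 20.0 to 22.5%. The lower figure assumes no further response at all, the extreme case for that share.

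A reader might go further and conclude that some baselines are already treated, or that diet effects will be counted as exercise. The documents do not support this: they give eligibility, not enrolment, and they do record weight and diet as potential confounders. The two influences would also run in opposite directions, so no net bias can be stated. This is a cheap improvement to a loosely worded criterion, not a flaw that invalidates the study.

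**What to change.** Split the criterion in section 4.3 into two.

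- *Diet:* exclude current participation, or participation in the 3 months before recruitment, in any diet or weight-loss programme, whatever its frequency.
- *Exercise:* keep a separate criterion. The sponsor should reconcile its cut-off with the training frequency in section 5.1 and Table 1; no particular value is proposed here.

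Reconcile the new wording with the instructions in sections 5.1 and 6.3.2, so that both ask the same thing about diet and weight.

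Verify it with a direct screening question on programme participation over the previous 3 months. The tools already planned cannot do this: the activity questionnaire in section 6.3.1 covers the intervention period, and the baseline dietary list in section 6.3.2 records four days of intake, not programme membership.

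The cost is one reworded criterion, one added screening question and a few more screen failures in a small recruitment.
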